### Sample size

2.2

Since there are no previous randomized controlled trials investigating this topic, the present study will be a pilot trial to provide effect size data for sample size calculations in subsequent large-scale randomized controlled trials. The sample size was not calculated based on a power calculation;^[20]^ instead, it was determined from estimates of the number of patients expected to participate and the minimum number of patients needed for an evaluation of the pragmatic purpose of the trial. Therefore, a total number of 60 participants, a sample size of 30 per group, will be recruited during the study, which is larger than the minimum number recommended for pilot studies.^[21]^

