### Statistical analysis

2.12

The SPSS statistical package (version 20.0, International Business Machines Corporation, China) will be used to analyze the data. The primary outcome will be analyzed by both intention-to-treat and per-protocol analysis. The data missing from intention-to-treat analysis will be replaced with the last measured value. The secondary outcomes will be analyzed by per-protocol analysis. Categorical variables will be displayed as percentages. Continuous variables will be presented as the mean ± standard deviation if the data fit a normal distribution in 2 groups. Otherwise, the data will be presented as the median (interquartile range). The Kolmogorov–Smirnov test will be applied as the normal distribution test for continuous variables. The *t*-test or Wilcoxon test will be used to compare the difference between groups according to the results of the Kolmogorov–Smirnov test. The results for categorical data will be compared using the chi-squared test. The statistical significance level will be set at 0.05 (2-sided), with a 95% confidence interval.

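### A Kolmogorov–Smirnov pre-test decides both the test and the summary statistics, so the pilot may report no mean difference or SD for the primary outcome, although its stated purpose is to inform the next sample size

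*Protocol article*

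**What the plan says.** Section 2.12 (Statistical analysis) sets out a data-driven rule for continuous variables.

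- Gate: "The Kolmogorov–Smirnov test will be applied as the normal distribution test for continuous variables".
- Summary if the gate is passed: "Continuous variables will be presented as the mean ± standard deviation if the data fit a normal distribution in 2 groups".
- Summary if it is not: "Otherwise, the data will be presented as the median (interquartile range").
- Between-group comparison, in a sentence that opens with the t-test: "test or Wilcoxon test will be used to compare the difference between groups according to the results of the Kolmogorov–Smirnov test".
- Error rate and interval: "The statistical significance level will be set at 0.05 (2-sided), with a 95% confidence interval". The quantity that the interval is for is not named.

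The rule makes no exception for the primary outcome, change in IPSS (section 2.9).

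Section 2.2 (Sample size) fixes the size, "a total number of 60 participants, a sample size of 30 per group, will be recruited during the study", and adds: "The sample size was not calculated based on a power calculation". It gives the purpose of the pilot as being "to provide effect size data for sample size calculations". The abstract, introduction and discussion repeat the sample-size aim. Nothing in the article says that means and SDs will be reported whatever the pre-test shows.

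**The concern.** The usual inputs for sizing a trial on a continuous change score are a mean difference and an SD. Section 2.12 withholds both from the report whenever the pre-test rejects and puts medians, interquartile ranges and a Wilcoxon result in their place. The rule for presenting results can therefore work against the purpose given in section 2.2.

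The second issue is prespecification. The quantity compared between arms (a difference in means or a shift in ranks) is settled by the same data that are then tested. If the gate is run afresh for each analysis, week 4 and week 8, or the intention-to-treat and per-protocol versions of the primary analysis, could be reported on different scales. The article does not say at what level the gate is applied, so this is a possibility and not a stated feature.

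This is a rule written into the article, not a detail left to a fuller document.

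**Working it through.** **Plan's own figure.** 2 × 30 = 60. No formula stands behind it, so there is nothing further to reproduce.

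**Inputs.** From the article: 30 per arm, two-sided 0.05, and the gate and two routes of section 2.12. I read the condition on two groups as requiring both arms to pass, so rejection in either arm sends the analysis to Wilcoxon. Assumed, because the article does not give them: the shape and SD of IPSS change, whole-number scores, a pre-test level of 0.05, and the version of the test. Both versions estimate the mean and SD from the sample. At n = 30 the critical distance is 0.159 with the Lilliefors correction and 0.242 without it.

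**Step 1. How often the mean and SD drop out of the report.** For exactly normal data and the corrected test, the expected rate is 1 − 0.95² = 0.0975. Simulation (20,000 trials per setting) gives 0.097. Share of trials with at least one arm called non-normal:

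| Assumed data, 30 per arm | Lilliefors | Uncorrected |
|---|---|---|
| Exactly normal | 10% | about 0% |
| Whole-number normal, SD 6 | 17% | under 0.5% |
| Whole-number normal, SD 5 | 20% | under 0.5% |
| Whole-number normal, SD 4 | 27 to 28% | 0.2% |
| Whole-number normal, SD 3 | 40% | about 0.5% |
| Gamma, skew 1 | 45% | 1.2% |
| Exponential, skew 2 | 95% | 22% |

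**Step 2. Whether the gate protects the t-test.** Type I error of the t-test used without a gate was 0.048 (normal), 0.049 (skew 1), 0.048 (skew 2) and 0.051 (whole-number scores, SD 3). The test holds its level at this size in every setting tried, so the gate adds no validity.

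**Step 3. Whether the gate distorts the test result.** Type I error of the gated procedure in the same four settings was 0.048, 0.053, 0.049 and 0.053. For a 2-point difference with whole-number scores and the Lilliefors gate, power compares as follows:

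- SD 3: 0.704 gated, 0.712 t-test (difference 0.008)
- SD 4: 0.472 gated, 0.474 t-test (difference 0.002)
- SD 6: 0.244 gated, 0.246 t-test (difference 0.002)

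The two procedures reached different conclusions in 1 to 3% of these trials, and in about 1% or fewer under no difference.

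**Step 4. What the missing SD costs someone who has only the published table.** That reader might approximate SD by IQR/1.35. At n = 30 per arm the average ratio of this approximation to the true SD was 0.955 (normal), 0.911 (skew 1) and 0.780 (skew 2), taken over all simulated trials and not only those that failed the gate. Required sample size is proportional to SD², so the planned N as a share of what is needed is:

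- 0.955² = 0.91
- 0.911² = 0.83
- 0.780² = 0.61

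With a reported SD pooled over 58 degrees of freedom and normal data, the 95% limits are √(58/χ²) times the estimate, that is 0.847 and 1.222. In terms of N this is 0.847² = 0.72 to 1.222² = 1.49 times. The uncertainty is wide, but it can be stated.

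**The case against.** The strongest reply is that the rule governs presentation only. Section 2.11 says the paper and electronic data are kept and that the study team can access them, and the discussion says the same team plans the follow-on comparison. It can compute any mean or SD it wants. This stands. A reader might infer that the pilot's main product is lost whenever the gate rejects, but the documents do not support that. The gap is in what is reported and in what is fixed beforehand.

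A reader might also infer that the route is close to arbitrary. That does not hold in general. With the corrected test, about 90% of exactly normal trials go to the t-test and about 95% of exponential trials go to Wilcoxon, so the test does discriminate. Intermediate rates arise with moderate skew or a small SD. Nor do ties by themselves cause rejection as a rule: at SD 5 and 6 they raise the rate from about 10% to 20% and 17%. The uncorrected test rarely rejects, though 22% for exponential data is not negligible. If that version is used on roughly normal scores, the reporting harm hardly arises.

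That the article does not name the version is not a fault here, since a full protocol or analysis plan could settle it. It only explains why the size must be given as a range.

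A further inference would be an inflated false-positive rate. Step 3 shows none of consequence.

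Lastly, section 2.2 promises effect size data without naming a mean difference and SD, and a later trial could be sized for a rank test. This is fair. Even so, a mean difference and SD are the most natural reading for a change in a symptom score, and medians with a Wilcoxon result do not directly supply them.

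**Conclusion.** The point holds as a defect of reporting and prespecification. As written, section 2.12 can leave the primary outcome without the mean difference and SD that section 2.2's purpose most naturally calls for, and the gate gives no validity in return.

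The chance of this depends on assumptions that the article does not settle. With a Lilliefors-type test it runs from about 10% (exactly normal) through 17 to 40% (whole-number normal scores, SD 6 to 3) and 45% (skew 1) to 95% (exponential). With the uncorrected test it is about 0.5% or less for whole-number scores with those SDs and 22% for exponential data. Type I error stays at about 0.05 and power within about 0.01 of the t-test. The sponsor does not lose the SD. A reader of the published table may, at a cost to the next trial's N that depends on skew (Step 4).

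The change should be made because it is nearly free and serves the stated aim, not because the test result would otherwise be unreliable.

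**What to change.** In section 2.12, remove the Kolmogorov–Smirnov gate and state instead:

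1. One primary between-group analysis, fixed in advance, that yields the mean difference in IPSS change with its 95% confidence interval. Adjustment for the baseline IPSS already collected is preferable, but the argument here does not depend on it.
2. Mean and SD by arm, reported for every continuous outcome whatever the shape of the data.
3. The Wilcoxon test as a sensitivity analysis that is always run, and median with interquartile range as added description.

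This costs a few sentences of analysis text. It needs no new data, visits or participants.

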### Recruitment and baseline assessment

2.3

Researchers will recruit participants from outpatient clinics at the Department of Acupuncture and Moxibustion, Beijing Hospital of Traditional Chinese Medicine, Capital Medical University, Beijing, China. Recruitment information will be posted in the hospital, containing a brief introduction of the study, participants, interventions, and contact details, which will be pre-approved by the Institutional Review Board.

Patients who are interested in participating in the study will be provided with detailed written and verbal information, and those who volunteer to enroll will be asked to complete an IPSS questionnaire and a 2-week nocturia record and undergo a routine urine test, prostate ultrasound, and uroflowmetry test as a baseline assessment. The results will be used to decide whether to include the patients in the study according to the inclusion and exclusion criteria. All recruited participants will give their written informed consent with a witness present prior to the beginning of the study, and subsequently complete a general information form, including name, gender, age, and medical history. All participants will be treated respectfully according to the Declaration of Helsinki and will be able to withdraw from the study at any time for any reason. Personal information regarding the participants will be collected and kept confidential.

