### Inclusion criteria

2.4

Patients are required to meet the following criteria:

(1)aged 40 to 80 years old;(2)diagnosed with BPH more than 3 months previously;(3)have a syndrome differentiation in traditional Chinese medicine conforming to “kidney yang deficiency;”^[22]^(4)have abstained from medication for BPH for longer than 6 months prior to the start of treatment;(5)have an IPSS score < 19 (mild-moderate BPH);(6)have a Q_max_ < 15 mL/s or a average flow rate  < 10 mL/s;(7)have stable life signs; and(8)participate voluntarily in the study and sign informed consent prior to treatment.

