### Outcome measures

2.9

The primary outcome is the change in IPSS over the 2-week baseline, 4-week treatment, and 4-week follow-up periods. The secondary outcomes are the changes in the mean number of nightly urinations, Q_max_ and average flow rate, and prostate volume as measured by a B-mode ultrasound device over the 2-week baseline, 4-week treatment, and 4-week follow-up periods. All outcome measures will be observed at baseline and 4 and 8 weeks following the beginning of treatment (Fig. 2).

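### The between-group test ignores baseline IPSS, which is already collected; adjusting for it is a nearly free gain in precision, of a size the protocol does not let us fix

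*Protocol article*

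**What the plan says.** - **Outcome** (section 2.9): "The primary outcome is the change in IPSS over the 2-week baseline, 4-week treatment, and 4-week follow-up periods". The timing is given as "All outcome measures will be observed at baseline and 4 and 8 weeks following the beginning of treatment".
- **Test** (section 2.12): a t-test is one option; the other branch reads "Wilcoxon test will be used to compare the difference between groups", with the choice resting on a Kolmogorov–Smirnov check of normality. No model, covariate or baseline adjustment is named.
- **Baseline value** (section 2.3): before inclusion, volunteers "will be asked to complete an IPSS questionnaire and a 2-week nocturia record", so baseline IPSS exists for every man randomised.
- **Entry limit** (section 2.4): men must "have an IPSS score < 19 (mild-moderate BPH"; no lower limit is stated.
- **Size and purpose** (section 2.2): "a total number of 60 participants, a sample size of 30 per group, will be recruited during the study", and "The sample size was not calculated based on a power calculation". The trial is meant to produce an effect size from which later, larger trials can be sized.

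**The concern.** A change score subtracts baseline with a fixed slope of 1. Unless the true slope of follow-up on baseline is close to 1, this over-corrects. If one arm happens to start higher, it tends to fall further by regression to the mean, and the change-score difference credits part of that fall to treatment. Over repeated randomisations this averages out to zero. In any single trial it is extra noise, tied to an imbalance that is visible in the baseline table.

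With 30 men per arm, precision is limited, and the estimate and its spread are the product the pilot is meant to deliver. The covariate that would remove this noise is already in the data.

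**Working it through.** **Inputs from the protocol.** 30 per arm, N = 60 (2 × 30 agrees with the stated total). No effect size, SD, power or correlation is given, so there is no planned figure to reproduce. Everything below beyond the 30 per arm rests on stated assumptions.

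**Notation.** s_b and s_f are the baseline and follow-up SDs, and r is their correlation within arm.

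**1. Direction, for any r and any SDs.**
- Var(change) = s_f² + s_b² − 2·r·s_f·s_b
- Var(ANCOVA residual) = s_f²·(1 − r²)
- Difference = (s_b − r·s_f)², which is never negative.

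Apart from the cost of estimating the slope, adjustment cannot lose precision. That cost is a variance factor of (N − 3)/(N − 4) = 57/56 = 1.018, about 1.8%. The critical t value moves only from 2.0017 (58 df) to 2.0025 (57 df).

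**2. Size if the SDs are equal (s_b = s_f = s, assumed).** The ratio is (1 − r²)/[2(1 − r)] = (1 + r)/2, then × 57/56. The standard error is √(variance × 2/30).

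| r (assumed) | (1 + r)/2 | with slope cost | SE, change score | SE, ANCOVA |
|---|---|---|---|---|
| 0.3 | 0.65 | 0.66 | 0.306 s | 0.248 s |
| 0.5 | 0.75 | 0.76 | 0.258 s | 0.226 s |
| 0.7 | 0.85 | 0.87 | 0.200 s | 0.186 s |

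A simulation of 20,000 trials per setting gave ANCOVA standard errors of 0.249, 0.225 and 0.185 s, with type I error of 0.047 to 0.050 for both methods. The change score breaks even at r = 2 × 56/57 − 1 = 0.965.

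**3. Size if the entry cap narrows baseline.** Selecting men on baseline IPSS shrinks s_b but, under a linear model, leaves the slope b of follow-up on baseline unchanged. Assume equal SDs of 1 before selection (so b = r before selection) and a baseline SD cut to 0.6. The residual variance stays 1 − r², and the change score adds (1 − r)² × 0.6² = (1 − r)² × 0.36.
- r = 0.3: 0.91/(0.91 + 0.1764) = 0.84
- r = 0.5: 0.75/(0.75 + 0.0900) = 0.89
- r = 0.7: 0.51/(0.51 + 0.0324) = 0.94

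These are before the slope cost; × 57/56 gives about 0.85, 0.91 and 0.96.

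**4. Chance imbalance.** The difference in baseline means has SD √(2/30) = 0.258 of a baseline SD. A difference d shifts the change-score estimate by (1 − r)·d under equal SDs, in favour of the arm that started worse. At r = 0.5 a difference of 0.258 SD shifts it by 0.5 × 0.258 = 0.129 SD. A difference beyond 0.25 SD arises in about 33% of trials.

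**5. Steps 2 and 4 describe one effect.** At r = 0.5 the squared imbalance shift is 0.129² = 0.0167, against a change-score variance of 0.258² = 0.0667. That is 25%, the same share that step 2 says adjustment recovers before the slope cost. The two should not be counted as separate losses.

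**The case against.** **The planned test is not wrong.** Under randomisation the unadjusted comparison of change scores is unbiased over repeated trials and holds its type I error. This stands. A reader might infer that the primary result would be invalid or systematically biased; the protocol does not support that. The shift in step 4 is conditional on an imbalance that may or may not occur.

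**The gain may be small.** A reader might take the equal-SD ratios as the expected benefit. The documents give no SDs, and admitting men on baseline IPSS itself makes equal SDs doubtful. Under step 3 the gain is roughly half or less of that in step 2. Nor can one infer from the missing lower limit that baseline will vary widely: no baseline SD is given, and an upper cap narrows the spread. This objection stands as to size, but not as to direction (step 1).

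**The Wilcoxon branch is not quantified.** Every figure compares ANCOVA with a t-test on change. If low baseline scores leave little room to improve, the relation with baseline may also be non-linear. Both points stand, and they are a reason to keep the planned tests as a sensitivity analysis.

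**Covariates may be left to an analysis plan.** A separate plan may exist. But the article does not leave the test open: it names it, and a primary adjusted model would depart from the text. The absence of any mention of stratification, by contrast, may be only condensation, and nothing here depends on it.

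**Conclusion.** The point holds as an improvement in efficiency, not as an error. Section 2.12 fixes an unadjusted comparison where a baseline-adjusted one would be at least as precise for any correlation and any SDs, apart from about 1.8% of variance.

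How much is gained is unknown. Over assumed correlations of 0.3 to 0.7, the variance ratio runs from 0.66 to 0.87 with equal SDs (slope cost included), and from 0.84 to 0.94 if selection cuts the baseline SD to 0.6 (slope cost excluded). A typical chance imbalance of 0.26 baseline SD would shift the change-score estimate by about 0.13 SD at r = 0.5 with equal SDs. These figures rest on a linear relation with a common slope and on the t-test branch. The case for acting is that the cost is close to nil and the pilot's stated product is an effect estimate.

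**What to change.** In section 2.12, make the main between-group analysis of the primary outcome a linear model of IPSS with arm and baseline IPSS as terms, at each planned time point (weeks 4 and 8). Using the change in IPSS as the response, with baseline still in the model, gives the same arm effect. Report the adjusted mean difference with its 95% CI. Do the same for nightly urinations, maximum and average flow rate, and prostate volume, each with its own baseline. Keep the t-test or Wilcoxon test as a sensitivity analysis.

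This leaves open which time point is primary, a choice the protocol does not make and this change does not need.

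Cost: a change of wording, one degree of freedom, about 1.8% of variance, and an assumption of linearity in baseline that should be checked. No new data are needed, and the SPSS package already named can fit the model.

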### Withdrawal and dropout

2.13

If participants use a combination of treatments that are prohibited by the study protocol, withdraw their consent, or cease communication, they will be excluded from the study. Researchers will report the reasons for withdrawal and dropout and acquire the time of last treatment and outcome measures where possible.

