#### Treatment group

2.8.1

Participants in the treatment group will receive fire needle therapy in the outpatient clinics of the Department of Acupuncture and Moxibustion at the hospital. Interventions will be performed in accordance with the STRICTA.^[23]^ All acupuncturists will be registered practitioners of traditional Chinese medicine with at least 5 years of clinical experience. The fire needle treatments and manipulations will be standardized among acupuncturists using specific training. Fire needles (0.65 × 45 mm; Beijing Zhongyan Taihe Medical Instrument Co., Ltd., Beijing, China) will be used. Other medication for BPH will be prohibited during the trial.

The following acupoints will be used: CV4 (*guanyuan*), CV2 (*qugu*), and bilateral ST28 (*shuidao*). All acupoints will be located according to the World Health Organization Standardized Acupuncture Points Location.^[24]^ The manipulation of fire needle therapy will be conducted according to Chinese national standard Standardized Manipulations of Acupuncture and Moxibustion.^[19]^ During treatment, participants will maintain a supine position after urination. The acupoints will be sterilized twice, from the center to the outside of an imaginary circle with a diameter of 5 cm, using 75% alcohol, or 0.5% to 1% iodophor if an alcohol allergy is present. After the skin is dry, the tip and middle of the fire needle will be heated until it turns red, following which the acupoint will be directly penetrated by the needle to a depth of 25 mm. The needle will be subsequently withdrawn without retention after the therapeutic depth has been reached, and the puncture wound will be covered with a sterile cotton ball to avoid bleeding.

Treatment will be conducted twice per week. Participants will be treated once a day and will receive a total of 8 treatment sessions over 4 consecutive weeks.

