#### Control group

2.8.2

Participants in the control group will receive watchful waiting, which is 1 of the conventional treatments suggested by both the Chinese and EAU Guidelines on the Management of Non-neurogenic Male LUTS.^[10,25]^ Watchful waiting and behavioral and dietary modifications are recommended as initial treatments for mild-moderate BPH (IPSS score < 19) in patients with non-bothersome LUTS. Accordingly, participants will receive education regarding BPH, reassurance regarding prognosis, and lifestyle advice once per week. Participants will receive a total of 4 outpatient visits over 4 consecutive weeks. Medication for BPH will be prohibited during the trial.

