#### Follow-up

2.8.3

After the 4-week treatment, follow-up will be conducted among all participants for 4 weeks. Fire needle therapy and BPH-related treatment are not permitted during follow-up.

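### Men who use prohibited BPH treatment after randomisation are excluded from the study, and the protocol does not secure their place in the ITT analysis or in the week-4 and week-8 assessments

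*Protocol article*

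**What the plan says.** Treatment for benign prostatic hyperplasia (BPH) is barred in both arms. For the treatment group (section 2.8.1): "Other medication for BPH will be prohibited during the trial". For the control group (section 2.8.2): "Medication for BPH will be prohibited during the trial". For the follow-up period (section 2.8.3): "Fire needle therapy and BPH-related treatment are not permitted during follow-up".

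Section 2.13 (Withdrawal and dropout) gives the consequence of breaking that bar. It applies to participants who combine "treatments that are prohibited by the study protocol, withdraw their consent, or cease communication, they will be excluded from the study". The next sentence reads "Researchers will report the reasons for withdrawal and dropout and acquire the time of last treatment and outcome measures where possible".

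Section 2.12 (Statistical analysis) defines the analyses: "The primary outcome will be analyzed by both intention-to-treat and per-protocol analysis". On missing values it adds "The data missing from intention-to-treat analysis will be replaced with the last measured value". For the other endpoints, "The secondary outcomes will be analyzed by per-protocol analysis".

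Outcomes are scheduled at baseline, week 4 and week 8 (section 2.9). The Discussion states that therapists and participants cannot be blinded.

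**The concern.** An ITT analysis keeps every randomised man in his arm. A rule that excludes men for something they do after randomisation sits badly with that, and section 2.13 does not say that it affects the per-protocol set only. It also treats a man who takes a BPH drug like one who withdraws consent or cannot be reached, although the first man can usually still complete an IPSS questionnaire and attend the visits.

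A man plausibly seeks BPH treatment because his symptoms trouble him. Participants know their arm, and controls receive education, reassurance and lifestyle advice only, so use may differ between arms. The missing values may then be informative. The trial's stated purpose is to supply effect-size data for later sample size calculations (section 2.2), so a distorted estimate would pass into the design of the next trial. The secondary outcomes have only a per-protocol analysis to rest on.

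**Working it through.** **Setting the sections side by side.** Take a man who starts a BPH drug in week 3.

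- Literal reading of section 2.13: he is out of the study, and nothing in section 2.12 brings him back. The set called ITT then omits a randomised man.
- Generous reading: his participation stops, but he stays in the ITT set under the last-value rule of section 2.12. Unless an extra measurement is obtained, his last scheduled value is baseline, so his change is baseline minus baseline = 0.
- If he starts the drug between weeks 4 and 8, the generous reading carries his week-4 value to week 8.

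On neither reading does the text commit the trial to his remaining scheduled assessments.

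**Size.** The protocol gives no SD, no rate of prohibited use and no link between use and outcome, so there is no plan figure to reproduce. Everything below is in SD units of IPSS change. The only document input is 30 men per arm (section 2.2).

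Standard error of the difference = √(2/30) = 0.258 SD.

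*Worst case.* Exactly the worst fraction p of one arm is dropped, with normal changes and nothing carried forward. Mean shift = φ(z₁₋ₚ)/(1 − p):

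- p = 5%: 0.109 SD
- p = 10% (three men): 0.195 SD, and 0.195/0.258 = 0.76 standard errors
- p = 20%: 0.350 SD

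*Less extreme cases.* Simulation of 40,000 trials, 30 per arm, true effect 0, mean change 0 in both arms. Assumed: a correlation r between use and a worse change, and the rates of use shown. Positive values make the control arm look better.

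| r | Use, control / needle | Men dropped | Baseline carried forward |
|---|---|---|---|
| 0 | all four pairs of rates | about 0 | about 0 |
| 0.5 or 0.8 | 10% / 10% | about 0 | about 0 |
| 0.5 | 10% / 0% | 0.097 | 0.087 |
| 0.5 | 20% / 5% | 0.122 | 0.089 |
| 0.5 | 30% / 10% | 0.151 | 0.087 |
| 0.8 | 10% / 0% | 0.156 | 0.140 |
| 0.8 | 20% / 5% | 0.191 | 0.139 |
| 0.8 | 30% / 10% | 0.241 | 0.137 |

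Hand check of the last row, with upper-tail densities φ = 0.348 at 30% and 0.1755 at 10%:

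- dropped: 0.8 × (0.348/0.70 − 0.1755/0.90) = 0.8 × (0.497 − 0.195) = 0.24
- carried forward: 0.8 × (0.348 − 0.1755) = 0.14

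In that row 21 controls and 27 needle patients remain if the men are dropped. Analysing all 60 on observed values gave a bias of about 0.00 in every row. The simulation gives the prohibited treatment no effect of its own. The carried-forward column treats every such man as leaving before week 4.

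**The case against.** A reader might infer that section 2.13 flatly contradicts section 2.12 and that the analysis called ITT cannot be one. The text does not prove this. Section 2.12 has a rule for filling values missing from the ITT analysis, which would have little use if every man who left also left the set, and section 2.13 asks for outcomes where they can be had. The two sections can be reconciled by taking exclusion to mean that participation stops. That much stands. It does not rescue the rule, because obtainable IPSS values may still be replaced by older ones.

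A reader might also infer that men are removed because of how they are doing. The trigger is use of a treatment, not a symptom score. The link to symptoms is a reasonable inference, but men enter with IPSS below 19 and more than 6 months off BPH medication, are followed for 8 weeks only, and no rate of use is given.

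Third, the 0.11 to 0.35 SD figures are tempting as an expected bias. They require the men dropped to be exactly the worst of one arm, with nothing carried forward.

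Finally, this is a pilot with no power calculation, and the article condenses a fuller protocol. Detailed definitions of analysis sets can properly sit elsewhere. But the exclusion rule is stated here, and it is the stated rule that needs changing. Excluding such men from the per-protocol set is normal and is not criticised.

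**Conclusion.** The point holds as a badly fixed rule, left unreconciled with the ITT promise; a strict contradiction is not established. Following section 2.13 as written can lose week-4 and week-8 IPSS values that could have been measured, in a trial whose participants are unblinded.

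The size cannot be known from the document. Under the assumptions shown:

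- about 0 if use is unrelated to outcome or equally common in both arms;
- roughly 0.1 to 0.24 SD if it is related to a worse outcome, commoner in controls, and the men are dropped;
- about 0.09 to 0.14 SD if baseline is carried forward;
- 0.11 to 0.35 SD only as a worst case.

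The standard error is 0.26 SD, so in these scenarios the shift is usually less than one standard error.

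The net direction is also unknown. A reader might assume that the rule flatters fire needle therapy. Losing worsening controls would work against it, while losing needle-arm non-responders would work in its favour.

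**What to change.** Amend sections 2.12 and 2.13 together so that:

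- use of prohibited treatment is recorded with date and type;
- these men stay in the scheduled week-4 and week-8 outcome assessments unless they withdraw consent to data collection;
- they are analysed in their randomised arm in the ITT analysis, using observed values;
- they are left out of the per-protocol analysis only;
- data already collected from men who withdraw are kept.

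This concerns data collection and analysis, and leaves the treatment prohibition as it is. The cost is a short amendment: the visits already exist and the sample size stays at 60.

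There is a downside to state in the plan. Values taken after prohibited treatment include that treatment's effect, so they do not recover what would have happened without it. The ITT result then estimates the effect of assignment regardless of such use, with the per-protocol result reported beside it.
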